| Review contraindications, inclusion and exclusion criteria    | X | X |     |                         |                         |                          |                           |                           |                  |                                         |                    |                                                                |  |
| Vaccination                                                   |   | X | X   |                         |                         |                          |                           |                           |                  |                                         |                    |                                                                |  |
| Vital signs^                                                  | X | X | (X) | (X)                     | (X)                     | (X)                      | (X)                       | (X)                       | X                |                                         |                    |                                                                |  |
| Telephone/Video call                                          |   |   |     |                         |                         |                          |                           |                           |                  | X                                       | As required        |                                                                |  |
| Ascertainment of adverse events                               |   | X | X   | X                       | X                       | X                        | X                         | X                         | X                | X                                       | X                  | X                                                              |  |
| Diary Cards §                                      |   | X | X   |                         |                         |                          |                           |                           |                  |                                         |                    |                                                                |  |
| Weekly household exposure questionnaire                       |   |   |     | ongoing                 |                         |                          |                           |                           |                  |                                         |                    |                                                                |  |
| Medical History (required at 1 timepoint prior to enrolment), | X | X | (X) | (X)                     |                         | (X)                      | (X)                       | (X)                       | (X)              | (X)                                     |                    |                                                                |  |

CONFIDENTIAL

| Attendance Number                                   | 1   | 2        | 3        | 4        | 5        | 6        | 7        | 8                  | COVID-19 Testing      | COVID-19 NAAT positive +7 days (Remote) | COVID-19 Follow-up | Extra Visit A |  |
|-----------------------------------------------------|-----|----------|----------|----------|----------|----------|----------|--------------------|-----------------------|-----------------------------------------|--------------------|---------------|--|
|                                                     |     |          |          |          |          |          |          |                    |                       |                                         |                    | Optional      |  |
| Physical Examination (if necessary)                 | (X) | (X)      | (X)      | (X)      |          | (X)      | (X)      | (X)                | (X)                   | (X)                                     |                    |               |  |
| Biochemistry, Haematology (mL)                      |     |          |          |          |          |          |          |                    |                       |                                         |                    |               |  |
| Exploratory immunology (mL)                         |     | up to 50 | up to 50 | up to 50 | up to 50 | up to 50 | up to 50 | up to 50           | up to 50 d |                                         |                    | up to 50      |  |
| PAXgenes                                            |     |          |          |          |          |          |          | (2.5) p | 2.5                   |                                         |                    |               |  |
| SARS-CoV-2 Serology                                 | 5   |          |          |          |          |          |          |                    |                       |                                         |                    |               |  |
| Nose/Throat Swab and/or saliva sample               |     |          |          |          |          |          |          |                    | X                     |                                         |                    |               |  |
| Stool sample a,b                         |     |          |          |          |          |          |          |                    |                       | (X)                                     | (X)                |               |  |
| Weekly PCR sample a                      |     |          | ongoing  |          |          |          |          |                    |                       |                                         |                    |               |  |
| Urinary bHCG (women of childbearing potential only) | X   | X        |          |          |          |          |          |                    |                       |                                         |                    |               |  |
| Blood volume per visit                              | 5   | 50       | 50       | 50       | 50       | 50       | 50       | 50                 | up to 52.5            |                                         |                    | up to 50      |  |
| Cumulative blood volume %                | 5   | 55       | 105      | 155      | 205      | 255      | 305      | 355                | 407.5                 | 407.5                                   |                    | 457.5         |  |

S = screening visit; (X) = if considered necessary; \*\* Timeline is approximate only. Exact timings of visits relate to the day. Where a second dose is administered, the window will apply to the time their last vaccination took place . ^Vital signs at screening or pre-enrolment assessment on D0 include pulse, blood pressure, temperature, respiratory rate +/- oxygen saturation. Only temperature will be routinely measured at subsequent follow-up visits. At COVID-19 testing visits a full set observations will be taken, including respiratory rate and oxygen saturation. % Cumulative blood volume for volunteers if blood taken as per schedule, and excluding any repeat safety blood test that may be necessary. Blood volumes may vary according to local site equipment and practices. a Subject to site capacity, sample and test availability. d Optional and subject to site capacity. § A subset of up to 1000 volunteers will be asked to fill an e-diary with reactogenicity symptoms for 7 days only in groups 4, 6, 9 and 10. p Pax genes sample at D364 to be done only on participants that have attended at least one COVID-19 testing visits within the trial testing visits, an extra 2.5mL should be added to the cumulative blood

CONFIDENTIAL

volume when this applies. b Optional Stool sample at approximately 7 days after onset of symptoms for those who have a positive SARS-CoV-2 NAAT test result and possibly again at 14 days after symptom onset if necessary.

CONFIDENTIAL

Table 9 Schedule of attendances for participants in group 5a1,5a2, 5b and 5c. Protocol V19: Unblinding / provision of treatment procedures will occur concurrently (Table 14) to these procedures.

| Attendance Number                                          | 1 s | 2 | 3       | 4   | 5   | 6   | 7   | 8   | 9   | COVID-19 Testing | COVID-19 NAAT positive + 7 days | COVID-19 Follow-up | Extra Visit A                                                  | Extra Visit B           |
|------------------------------------------------------------|----------------|---|---------|-----|-----|-----|-----|-----|-----|------------------|---------------------------------|--------------------|----------------------------------------------------------------|-------------------------|
|                                                            |                |   |         |     |     |     |     |     |     |                  |                                 |                    | Optional                                                       | Optional                |
| Timeline**(days)                                           | ≤ 90           | 0 | 3       | 7   | 14  | 28  | 56  | 182 | 364 | As required      | 7 days post NAAT positive       |                    | At time of early unblinding before receipt of deployed vaccine | At earliest possibility |
| Time window (days)                                         |                |   | ±1      | ±2  | ±3  | ±7  | ±7  | ±14 | ±30 | N/A              | -2,+7                           |                    | N/A                                                            | ≥4 weeks post prime     |
| Informed Consent                                           | X              |   |         |     |     |     |     |     |     |                  |                                 |                    |                                                                |                         |
| Review contraindications, inclusion and exclusion criteria | X              | X |         |     |     |     |     |     |     |                  |                                 |                    |                                                                |                         |
| Vaccination                                                |                | X |         |     |     |     |     |     |     |                  |                                 |                    |                                                                | X                       |
| Vital signs                                                | X              | X | (X)     | (X) | (X) | (X) | (X) | (X) | (X) | X                |                                 |                    |                                                                |                         |
| Telephone/Video call                                       |                |   |         |     |     |     |     |     |     |                  | X                               | As required        |                                                                |                         |
| Ascertainment of adverse events                            |                | X | X       | X   | X   | X   | X   | X   | X   | X                | X                               | X                  | X                                                              | X                       |
| Diary cards provided                                       |                | X |         |     |     |     |     |     |     |                  |                                 |                    |                                                                |                         |
| Diary cards collected                                      |                |   |         |     |     | X   |     |     |     |                  |                                 |                    |                                                                |                         |
| Weekly household exposure questionnaire                    |                |   | ongoing |     |     |     |     |     |     |                  |                                 |                    |                                                                |                         |

CONFIDENTIAL

| Attendance Number                                   | 1 S | 2        | 3       | 4        | 5        | 6        | 7        | 8        | 9        | COVID-19 Testing | COVID-19 NAAT positive + 7 days | COVID-19 Follow-up | Extra Visit A | Extra Visit B |
|-----------------------------------------------------|----------------|----------|---------|----------|----------|----------|----------|----------|----------|------------------|---------------------------------|--------------------|---------------|---------------|
|                                                     |                |          |         |          |          |          |          |          |          |                  |                                 |                    | Optional      | Optional      |
| Medical History, Physical Examination               | (X)            | (X)      | (X)     | (X)      | (X)      | (X)      | (X)      | (X)      | (X)      | (X)              | (X)                             |                    |               |               |
| Biochemistry, Haematology (mL)                      | 5              | (5)*     | 5       | 5        |          | 5        |          |          |          |                  |                                 |                    |               |               |
| Hep B, C and HIV serology                           | 5              |          |         |          |          |          |          |          |          |                  |                                 |                    |               |               |
| Exploratory immunology (mL) e            |                | up to 55 |         | up to 50 | up to 50 | up to 50 | up to 50 | up to 50 | up to 50 | up to 50         |                                 |                    | up to 50      | up to 50      |
| SARS-CoV-2 Serology                                 | 5              |          |         |          |          |          |          |          |          |                  |                                 |                    |               |               |
| PAXgenes                                            |                | 2.5      |         |          |          |          |          |          |          | 2.5              |                                 |                    |               |               |
| Nose/Throat Swab and/or Saliva Sample               |                |          |         |          |          |          |          |          |          | X                |                                 |                    |               |               |
| Stool sample a,b                         |                |          |         |          |          |          |          |          |          |                  | (X)                             | (X)                |               |               |
| Weekly PCR sample                                   |                |          | ongoing |          |          |          |          |          |          |                  |                                 |                    |               |               |
| Urinary bHCG (women of childbearing potential only) | X              | X        |         |          |          |          |          |          |          |                  |                                 |                    |               | X             |
| HLA typing (mL)                                     |                | 4        |         |          |          |          |          |          |          |                  |                                 |                    |               |               |
| Blood volume per visit                              | 15             | 61.5     | 5       | 55       | 50       | 55       | 50       | 50       | 50       | up to 52.5       |                                 |                    | up to 50      | up to 50      |
| Cumulative blood volume %                | 15             | 76.5     | 81.5    | 136.5    | 186.5    | 241.5    | 291.5    | 341.5    | 391.5    | 444              | 444                             |                    | 494           | 494           |

S = screening visit; (X) = if considered necessary; \*\* Timeline is approximate only. Exact timings of visits relate to the day on enrolment, ie, each visit must occur at indicated number of days after enrolment  $\pm$  time window. ^Vital signs at screening or pre-enrolment assessment on D0 include pulse, blood pressure, temperature, respiratory rate +/- oxygen saturation. Only temperature will be routinely measured at subsequent follow-up visits. At COVID-19 testing visits a full set observations will be taken, including respiratory rate and oxygen saturation. % Cumulative blood volume for volunteers if blood taken as per schedule, and excluding any repeat safety blood test that may be necessary. Blood volumes may vary according to local site equipment and practices. \*Safety bloods should only be repeated at vaccination day if there is a period greater than 2 weeks between screening and vaccination visit;

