#### **6.3.1 Inclusion Criteria**

The volunteer must satisfy all the following criteria to be eligible for the study:

- Adults aged 18 - 55 years (groups 4, 5, 6 and 11)
- Adults aged 56-69 years (groups 1, 7, and 9)

- Adults aged 70 years and older (groups 2, 8, and 10)
- Able and willing (in the Investigator's opinion) to comply with all study requirements.
- Willing to allow the investigators to discuss the volunteer's medical history with their General Practitioner and access all medical records when relevant to study procedures.
- For females of childbearing potential only, willingness to practice continuous effective contraception (see below) during the study and a negative pregnancy test on the day(s) of screening and vaccination.
- Agreement to refrain from blood donation during the course of the study.
- Provide written informed consent.

Additional Inclusion criteria to Group 12 (HIV sub-study):

- HIV positive
- Receiving antiretroviral therapy
- Undetectable HIV viral load
- CD4>350 cells/mL

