### 6.3.3 Re-vaccination exclusion criteria

The following AEs associated with any vaccine, or identified on or before the day of vaccination constitute absolute contraindications to further administration of an IMP to the volunteer in question. If any of these events occur during the study, the subject will not be eligible to receive a booster dose and will be followed up by the clinical team or their GP until resolution or stabilisation of the event:

- Anaphylactic reaction following administration of vaccine
- Pregnancy. An exception to this will be prior to receipt of a booster dose at extra visit B. If a pregnant woman has discussed vaccination with their usual clinician (e.g. GP) and chooses to receive a COVID-19 vaccination, this may be administered by the trial team as part of extra visit B (*Protocol 19.0:*) or as part of the provision of treatment to controls.
- Any AE that in the opinion of the Investigator may affect the safety of the participant or the interpretation of the study results

Participants who develop COVID-19 symptoms and have a positive NAAT test after the first vaccination can only receive a booster dose after a minimum 4 weeks interval from their first NAAT positive test, provided their symptoms have significantly improved. The decision to proceed with booster vaccinations in those cases will be at clinical discretion of the investigators. For participants who are asymptomatic and have a positive NAAT test, a minimum of 2 weeks from first NAAT positivity will be required before boosting.

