### **6.5 Pregnancy**

Should a volunteer become pregnant during the trial, no further study IMP will be administered\* (see below for exception). She will be followed up for clinical safety assessment with her ongoing consent and in addition will be followed until pregnancy outcome is determined. We would not routinely perform venepuncture in a pregnant volunteer unless there is clinical need. Given that no routine bloods will be drawn from pregnant volunteers, follow-up visits may be conducted over the phone/video consultation in order to minimise contact and exposure from SARS-CoV-2 in pregnant volunteers

\* The current UK national vaccination policy advice is that pregnant women may receive the vaccine as part of the national rollout of COVID-19 vaccines in certain circumstances. The decision on

whether COVID-19 vaccination should be recommended for any pregnant participants in the trial will not be taken by trial teams. However, if after discussion of the risk and benefits of COVID-19 vaccination with their usual clinician (e.g. GP), a pregnant participant chooses to have a COVID-19 vaccination during pregnancy, this may be administered by the trial team as part of extra visit B, although no blood samples will be drawn.

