- **Immunology;** Immunogenicity will be assessed by a variety of immunological assays. This may include antibodies to SARS-CoV-Spike and non-Spike antigens by ELISA, ex vivo ELISpot assays for interferon gamma and flow cytometry assays, neutralising and other functional antibody assays and B cell analyses, virus neutralising Ab (NAb) assays against live and/or pseudotype SARS-CoV-2 virus. Other exploratory immunological assays including cytokine analysis and other antibody assays, DNA analysis of genetic polymorphisms potentially relevant to vaccine immunogenicity and gene expression studies amongst others may be performed at the discretion of the Investigators. Further exploratory immunology assays may be performed at the discretion of the Investigators on HIV and non-HIV cohorts, including, but not limited to: T cell Proliferative responses to SARS-CoV-2 antigen; T cell cross-reactivity to circulating common cold coronaviruses; Multiparameter immunophenotyping by CyTOF; BCR and TCR repertoire analysis; Serum analysis by Luminex (including inflammatory, anti-inflammatory and adaptive cytokines, chemokines, growth factors and antimicrobial proteins); HIV viral reservoir; amongst others.

- **Stool samples;** SARS-CoV-2 NAAT, infectivity assays, calprotectin, and other exploratory immunology and microbiology assays may be conducted in a subset of participants, subject to site capacity, sample and test availability
- **Mucosal Immunity Swabs (Synthetic Absorptive Matrix [SAM]);** an assessment of mucosal immunity will be conducted in a subset of participants, subject to site capacity, sample and test availability.
- **SARS-CoV-2 weekly PCR sample;** weekly nose/throat swabs will be processed via the Department of Health and Social Care's community testing programme.

At each site:

- **Urinalysis;** For female volunteers of child bearing potential only, urine will be tested for beta-human chorionic gonadotrophin ( $\beta$ -HCG) at screening (when applicable) and immediately prior to vaccination. Where local policies require, a serum  $\beta$ -HCG may replace urinary test.
- **Serum;** Samples may be centrifuged at local sites and shipped to University of Oxford laboratories or elsewhere for analysis.

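### The schedules for groups 4b, 9, 10 and 11 show neither a contraindication review nor a pregnancy test at the second vaccination, out of line with the text and with the other two-dose schedules

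*Protocol*

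**What the plan says.** **Text.** Section 6.3.1 makes it an inclusion criterion for women of childbearing potential to have "a negative pregnancy test on the day(s) of screening and vaccination". Section 7.2 places the urine test "at screening (when applicable) and immediately prior to vaccination". Section 6.3.3 lists events which, if "identified on or before the day of vaccination constitute absolute contraindications to further administration of an IMP". The list covers anaphylaxis after vaccine, pregnancy (with an exception for Extra Visit B and for provision of treatment to controls) and any adverse event that the investigator thinks may affect safety or interpretation. The section also sets waiting times after a positive NAAT. Section 6.5 states: "Should a volunteer become pregnant during the trial, no further study IMP will be administered", with the same exception for Extra Visit B. Section 9.14.1 adds individual stopping rules for the prime-boost groups.

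**Tables.** Sections 7.1 and 7.3 send sites to the schedules of attendances for the procedures at each visit. The relevant rows are Vaccination, "Review contraindications, inclusion and exclusion criteria" and "Urinary bHCG (women of childbearing potential only". In Tables 8, 11 and 12 the last two are marked at attendances 1 and 2 only, while Vaccination is marked again later.

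**The concern.** The protocol gives two answers to what must be done before the second dose in these groups. A site following the text would test women of childbearing potential on the boost day. A site following the table would not. No precedence rule between text and table is stated.

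The review row raises a related problem. Several bars on a further dose can arise only after the prime: a reaction to the first dose, a new pregnancy, a recent positive NAAT, or a related Grade 3 event. Without a review marked at the boost visit, these rules have no scheduled point at which they are formally checked, and sites may record the check differently. It is also unclear whether a boost given without a test or review is a deviation under section 12.4: against the text a missing test is one, against the table it is not.

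**Working it through.** The protocol gives no figure to reproduce. The check is a cell-by-cell reading of three rows at each second-dose visit.

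| Schedule | Groups | Second-dose attendance | Vaccination | Contraindication review | bHCG |
|---|---|---|---|---|---|
| Table 8 | 4b | 3 | X | blank | blank |
| Table 11 | 9, 10 | 3 (V2) | X | blank | blank |
| Table 12 | 11 | 4 (V2) | X | blank | blank |
| Table 5 | 1b, 2b, 5d, 7b, 8b | 6 (V2) | X | X | X |
| Table 6 | 5e, 5f | 6 (V2) | X | X | X |
| Table 10 | 4c, 6b, boosts of 1a, 2a, 5a | 1 (V2) | X | X | X |
| Table 13 | 12 | 6 (V2) | X | X | X |

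The footnotes to Tables 8, 11 and 12 do not supply the missing checks. Table 10 does not cover groups 4b, 9, 10 or 11, so it does not close the gap.

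**Extra Visit B.** Vaccination is marked in Tables 4, 5, 7, 9 and 11, and the review is blank in all five. The pregnancy test is marked in Tables 4, 5, 7 and 9 and blank in Table 11.

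**Is the difference deliberate?** Nothing says so. Where the protocol drops pregnancy testing, in the provision of ChAdOx1 nCoV-19 to controls (the Table 14 in section 7.3.3), it says so and gives the reason. That statement does not cover the planned second study dose, and the same table still marks a contraindication review at both prime and boost.

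**Size, pregnancy test.** Group 4b is up to 50 + 50 = 100, and group 11 is up to 60. Together 100 + 60 = 160 participants aged 18-55. This is an upper bound: it includes men and, in 4b, the MenACWY arm. Groups 9 and 10 start at age 56.

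**Size, review.** All four groups are affected: 100 (4b) + 2 × 1,000 (9 and 10) + 60 (11) = 2,160 planned second-dose visits. Groups 9 and 10 may vary by 10%, which gives 1,800 to 2,200 for them and 1,960 to 2,360 in total. Half of groups 4b, 9 and 10 receive MenACWY. This counts visits without a scheduled review, not participants dosed against a contraindication.

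**The case against.** - **The text does not literally require a review before each dose.** This stands in part. The cited sentences of 6.3.1 and 7.2 concern only the pregnancy test, 6.3.3 lists contraindications without prescribing a review visit, and the explicit eligibility review in 7.3.2 sits under Day 0. The direct contradiction is therefore the pregnancy test. The review is a gap between rules that must be applied and a schedule that does not say when. The wording in 6.3.1 allows for more than one day, and 7.2 is not limited to the first dose.

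- **A reader might infer that contraindications are not looked for at all before the boost.** The documents do not support that. Adverse-event ascertainment is marked at the second-dose visit in Tables 8, 11 and 12 and at every Extra Visit B, and vital signs, history and examination are available at those second-dose visits if considered necessary. Two of the three listed items in 6.3.3 are adverse events, so they are partly covered.

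- **A reader might infer that the mismatch changes eligibility for the primary analysis set.** It does not. Eligibility for a second dose is set for every group by 6.3.3, 6.5 and 9.14.1, and the tables state no rival rule. The primary analysis compares vaccine with control among two-dose recipients whose booster was high-dose. Group 4b has a 2.2 × 10^10 vp (qPCR) boost and was added for immunogenicity, and group 11 is open-label without a control. Groups 9 and 10 contribute, and there the pregnancy test hardly arises.

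- **Pregnancy is excepted at Extra Visit B.** True, and the test is marked there in four of the five tables. The exception covers pregnancy only, so the other contraindications still apply with no review marked.

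**Conclusion.** The inconsistency is real and sits in three schedules plus the Extra Visit B columns. The unmarked pregnancy test contradicts 6.3.1 and 7.2 and has practical weight for up to 160 participants in groups 4b and 11; the affected number is smaller and cannot be derived from the protocol. The unmarked review leaves 6.3.3 and 9.14.1 without a scheduled formal check in all four groups, partly offset by adverse-event ascertainment.

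This is a consistency and safety-procedure point that should be corrected. It is not a threat to the efficacy estimate. It assumes that the blank cells are as printed; the comparison with Tables 5, 6, 10 and 13, read in the same way, supports this. How many second doses remain to be given is not stated, though section 5.4 allows boosters to continue at any age.

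**What to change.** Reconcile Tables 8, 11 and 12, and the Extra Visit B columns of Tables 4, 5, 7, 9 and 11, with sections 6.3.1, 6.3.3, 6.5, 7.2 and 9.14.1, so that tables and text state the same pre-dose checks at each visit where a vaccine is given. If a check is meant to differ for a group or for Extra Visit B, say so in a footnote with the reason, as is done for provision of treatment to controls. Which clinical rule should prevail is for the sponsor and investigators to decide. The cost is a table correction in an amendment, with negligible site work and no change to sample size or analysis.
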